### **Objective and Overview of the Study**

to conduct a pilot study to improve insulin sensitivity, prevent weight gain and reduce visceral adiposity in African-American, Hispanic, South Asian, and other high risk populations of normoglycemic, hyperinsulinemic women with midlife weight gain. Enhance the Metabolic Profile of Women with Insulin Resistance (EMPOWIR) will compare three treatment protocols in a randomized, double-blind, clinical trial and optional, post-treatment surveillance analysis.

The objective of the study is to compare the effect of carbohydrate modified diet alone and in combination with metformin (MF) and Avandamet® (metformin plus rosiglitazone (RSG)) on insulin parameters in a wide range of ethnically and economically diverse non-diabetic women (aged 35-55) who meet study selection criteria seen at three academic medical centers: The Hispanic Center of Excellence and The Menopause Research and Treatment Center at Albert Einstein College of Medicine/Montefiore Hospital; The Diabetes Center of Excellence at The University of Tennessee; and The Center for Diabetes and Endocrine Care at New York Medical College/Westchester Medical Center and their affiliated practices. All women will receive the calorie-reduced, carbohydrate modified (sugar restricted, low glycemic index) diet based on large servings of vegetables, fruits, lowfat proteins and dairy products and limited refined carbohydrates and treats. Devised 30 years ago and field-tested in more than a thousand patients in the past decade, this dietary program integrates scientific findings and recommendations from numerous current research studies.

A 3-arm trial will be conducted in a final study population of 75 normoglycemic hyperinsulinemic women (glucose-mediated AUC-insulin >100mU/ml) randomized (Phase 1) to an initial 6-month treatment of study diet, with placebo, metformin, or Avandamet®. Subjects initially randomized to placebo arm will be reassigned after 6 months to one of the two active treatment arms (Phase 2).

Initial funding will be used to develop a core program to facilitate additional research at

[figure not shown]

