| 
Study Design
          | 
Overview
<small>Please see attached Study Flow Chart</small>
 
Chart review of patients at the 3 study Centers and their affiliated General Medical and Gynecology practices and public announcements will be used to identify non-diabetic women who meet selection criteria who will be invited to participate in the study. After obtaining consent, and additional screening for suitability, 80 patients will undergo glucose tolerance testing and additional tests to determine if they meet study inclusion and exclusion criteria. Following a 1-month lead-in phase, an initial study population of 75 women from 3 clinical sites will be randomized to placebo (diet and lifestyle modification) or one of two active study treatment arms for a 6-month study (Phase 1); patients in the diet plus placebo group will then be crossed over to one of the two active study arms for a 2nd six months (Phase 2).
 |
| 
Inclusion / Exclusion
 | 
Inclusion Criteria
 
 
1. Healthy, non-diabetic women with "≥20 pound weight gain since their twenties"
 
2. Age: 35-55
 
3. Peri-menopausal ( FSH ≥25 on day 2-3 of cycle) or postmenopausal status
 
4. Body Mass Index (BMI) 25-35 kg/m^2
 
5. Either:             
 
(a). a single blood pressure recording ≥135/85 or the use of blood pressure medication
 
OR
 
(b) HDL≤50mg/dl or triglycerides ≥150 mg/dl or the use of lipid modifying medication
 
 
 
7. Area-under-the-curve (AUC-)insulin level ≥100μU/ml along with normal fasting (≤100 mg/dl) & postprandial (≤200 mg/dl) glucose determinations following a 75-gram standard oral glucose tolerance test.
 
 
Exclusion Criteria
                                                             |

[figure not shown]

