| Study Endpoints/
Objectives                    | 
The study objective is to compare the effects of metformin, and Avandamet® on markers of insulin resistance – fasting, peak (1-hour) and AUC-insulin, and HOMA-R, and body fat distribution in hyperinsulinemic, peri- and post-menopausal women with progressive weight gain (Syndrome W) prior to the onset of overt glycemic abnormalities or full-blown Metabolic Syndrome.
 
The primary outcome variables will be 1-year change in fasting and 1-hour insulin (as noted below.)
                                                                                                                                                                                                                                                                                                                                                                                                                                                                                                                                              |

|                                                                                |                                                                                                                                                                                                                                                                                                                                                                                                                                                       |
|--------------------------------------------------------------------------------|-------------------------------------------------------------------------------------------------------------------------------------------------------------------------------------------------------------------------------------------------------------------------------------------------------------------------------------------------------------------------------------------------------------------------------------------------------|

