|-------------------------------------------|---------------------------------------------------------------------------------------------------------------------------------------------------------------------------------------------------------------------------------------------------------------------------------------------------------------------------------------------------------------------------------------------------------------------------------------------------------------------------------------------------------------------------------------------------------------------------------------------------------------------------------------------------------------------------------------------------------------------------------------------------------------------------------------------------------------------------------------------------------------------------------------------------------------------------------------------------------------------------------------------------------------------------------------------------------------------------------------------------------------------------------------------------------------------|
|                                           | 
profiles at the 1, 2-, 3-, 6- and 12-month study visits (noted in Table 1).
 
GTT and insulin response curves will be obtained at baseline and at the end of 6 and 12 months in study completers.
 
Adverse events will be monitored and recorded by the study coordinators in accordance with IRB governance and guidelines at the three participating institutions. Serious adverse events (hospitalization, death or pregnancy) will be reported to GSK within 24 hours of obtaining SAE information.
                                                                                                                                                                                                                                                                                                                                                                                                                                                                                                                                                                                                                                           |

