| Outcome Parameters / Analytical Endpoints | 
The primary outcome variables are change from baseline in fasting and one-hour insulin at 1 year. Secondary outcome measures are 6 and 12 month change from baseline in body weight, CT scan-determined visceral adipose tissue other fat compartments, and relevant ratio's; total and multimeric adiponectin; and other cardiovascular risk and inflammatory markers, including lipids, c-reactive protein, TNF-<math>\alpha</math>, leptin, ghrelin, and resistin; and IGF-1 and IGF-binding proteins.
                                                                                                                                                                                                                                                                                                                                                                                                                                                                                                                                                                                                                        |
| Statistical Analysis Plan                 | 
Power Calculations and Assumptions
 
Three power calculations were performed incorporating the significance levels and sample size of TZD-based interventions in recently reported studies and comparator trials. A initial sample size of 25 per group is a realistic estimate and is based on the following assumptions:
 
 
1. Placebo treatment even with intensive dietary intervention (which will not be provided after the lead-in phase of EMPOWIR) has low rates of weight loss and high drop out rates at 6 and 12 months of study follow-up in the majority of published studies
 
2. data from observational and population based studies show annual weight gain in women in the study age range and BMI category
 
3. Metformin has a large treatment effect in hyperinsulinemic women and, in combination with hypocaloric carbohydrate modified diet, reduced fasting insulin by 25-40% and 1-hour (peak) insulin by 50% in our preliminary data. (with a mean body weight change 12.5% at 1-year).
 
4. Enrollment goals assume 10% drop out during Phase 2
 
 |

[figure not shown]

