#### Summary of sample size calculations:

The study design comprises 3 groups in one pre-treatment (Phase 1) and one post-treatment (Phase 3) measurement of outcome. Preliminary data from our open label use of metformin and other randomized clinical trials suggest that metformin affords large treatment effects. Nonetheless, as the large effect may be due in part to placebo, we will structure our sample size to detect more moderate treatment effects. Using an analysis of covariance, a sample size of 60 patients (20 per group) will provide at least 80% power to detect a moderate to large effect size ( $f=.38$ ) for a two-sided test of significance at a critical value of .05. While 20 patients per group are required to meet the anticipated effects, we will target 25 per group to allow for 20% attrition. The proposed attrition rate is less than rates reported in research studies of other medications evaluated for weight reduction, such as sibutramine (32%) and xenical (24%). However, the rate reflects attrition rates from our own preliminary data and from other published studies of patients treated with metformin analyzed using an intention-to-treat or comparable analysis such as studies of obesity in women, and children, PCOS, and HIV-related lipodystrophy.

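### The primary outcome is read at 1 year, but the whole placebo arm moves to active drug at month 6, so no diet-alone comparator is left at the primary visit

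*Protocol*

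**What the plan says.** **Treatment.** The Study Design overview randomises women to placebo, metformin or Avandamet for a 6-month Phase 1. After that, "patients in the diet plus placebo group will then be crossed over to one of the two active study arms" for a second six months (Phase 2). Objective and Overview of the Study says the same, and neither place states an exception.

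**Primary outcome.** Under Study Endpoints/Objectives the primary variables "will be 1-year change in fasting and 1-hour insulin". Under Outcome Parameters / Analytical Endpoints they "are change from baseline in fasting and one-hour insulin at 1 year". No 6-month insulin outcome is named as primary, and insulin is not in the secondary list.

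**Objective.** Objective and Overview of the Study sets out to "compare the effect of carbohydrate modified diet alone and in combination with metformin (MF) and Avandamet". Study Endpoints/Objectives words the aim differently, as a comparison of metformin and Avandamet, and does not mention diet alone.

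**Sample size.** Summary of sample size calculations describes three groups with one pre-treatment and one post-treatment measurement, 20 completers per group, f = .38, two-sided .05 and at least 80% power. The effect was lowered from open-label experience because, "as the large effect may be due in part to placebo, we will structure our sample size to detect more moderate treatment effects".

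**Assessments and analysis.** Under Study Variables, "GTT and insulin response curves will be obtained at baseline and at the end of 6 and 12 months". The Statistical Plan compares group changes at both 6 and 12 months.

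**The concern.** These elements do not fit together. The objective and the three-group sizing need a diet-plus-placebo group at the time of the primary measurement, and the treatment schedule removes that group six months earlier.

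At 1 year the women randomised to placebo are a mixture of women with six months of metformin and women with six months of Avandamet. Setting them against the original active arms asks whether 12 months of drug differs from 6 months after a delayed start. The comparison gets worse as the drugs get better: the faster and more complete the response, the closer the former placebo group comes to the active arms. A null primary result could therefore come from an effective drug.

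Metformin versus Avandamet among women randomised to those drugs at baseline remains a fair comparison at 1 year, but it is a two-group question that the sample size does not address.

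**Working it through.** **Inputs from the protocol.** Three groups, 20 completers each (N = 60), f = .38 and two-sided alpha .05 (Summary of sample size calculations). Switch of the placebo arm at month 6 (Study Design). Primary visit at 1 year (Outcome Parameters / Analytical Endpoints).

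**Inputs assumed.** The share p of the 12-month drug effect that switched women have reached by month 12, shown from 0 to 1. The pattern of arm means, since the protocol gives no means or SDs. An equal split of switched women between the two drugs. The active arms are taken to continue to month 12, which the protocol implies but does not state in the text at hand.

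**The protocol's own figures.** Attrition: 20/(1 − 0.20) = 25 per group, 75 in all, which agrees. Power: noncentral F with 2 and 57 degrees of freedom and λ = N·f² = 60 × 0.38² = 8.66 gives 73.0%. An ANCOVA divides the error variance by 1/(1 − r²), where r is the baseline-outcome correlation, so λ = N·f²/(1 − r²). This gives 80.6% at r = 0.4 and 85.1% at r = 0.5. The stated 80% is therefore reachable with an unstated correlation of about 0.4. That gap is a separate matter, so both versions are carried below.

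**Scheduled exposure to placebo.** 25 of 25 up to month 6; 0 of 25 at month 12.

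**Pattern A: both drugs equally effective.** Standardised effects are 0, d, d, so f = d·√2/3. Setting f = .38 gives d = 0.806 SD. At month 12 the means are p·d, d, d, so f = .38(1 − p).

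| p | f at month 12 | Power, r = 0 | Power, r = 0.5 |
|---|---|---|---|
| 0 | .38 | 73% | 85% |
| .5 | .19 | 23% | 30% |
| .75 | .095 | 9% | 11% |
| 1 | 0 | 5% | 5% |

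**Pattern B: metformin half as effective as Avandamet.** Effects are 0, d/2, d, so f = d·√(1/6). Setting f = .38 gives d = 0.931 SD. Switched women average 0.75·p·d, so the month-12 means are 0.75·p·d, 0.5·d, d.

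| p | f at month 12 | Power, r = 0 | Power, r = 0.5 |
|---|---|---|---|
| 0 | .38 | 73% | 85% |
| .5 | .25 | 38% | 49% |
| 1 | .19 | 23% | 30% |

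At p = 1 in Pattern B, the remaining signal comes only from the difference between the two drugs, not from drug versus diet.

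**If the 1-year primary is meant as metformin versus Avandamet.** Reading f = .38 as a two-group effect gives d = 2 × .38 = .76. A t test with 20 per arm has 65% power, and 29 per arm are needed for 80%. Under Pattern B the difference between the drugs is only 0.931/2 = 0.466 SD. Power at 20 per arm is then 30%, and about 74 per arm are needed. Under Pattern A the difference is zero.

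**The case against.** **The two-drug reading.** Study Endpoints/Objectives gives the aim as metformin against Avandamet, and a 1-year primary suits that, because the comparison stays randomised. This is a fair reading of that one cell. It still conflicts with the diet-alone objective stated earlier and with sizing for three groups, so the protocol would need to choose and re-size.

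**The 6-month comparison already exists.** The test is scheduled and the Statistical Plan compares groups at 6 months. This stands: the trial can answer the diet-alone question with all arms intact. What is wrong is that the comparison is not the primary one.

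**Weak evidence that sizing rests on placebo.** The power assumption that placebo "has low rates of weight loss and high drop out rates at 6 and 12 months of study follow-up" refers to weight loss and drop-out in published studies, not to an insulin contrast in this trial. That is correct, so it carries little weight here. The three-group calculation and its allowance for a placebo effect carry the point.

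**The power figures rest on assumptions.** True. The share p, the effect patterns and the equal split are not in the protocol, and the 5% figure follows by construction once drugs are equal and catch-up is complete. A plain ANOVA also understates power if the baseline covariate is useful. The r = 0.5 columns allow for this, and the loss remains. The figure of 29 per arm depends on carrying f = .38 over to two groups, and Pattern B shows how far it can move.

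**Last observation carried forward.** Placebo women who leave before the switch would carry a placebo value to month 12. They are a self-selected subset and do not restore a randomised placebo arm.

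**Unseen attachments.** The flow chart and dosing table may state that the active arms continue. Placebo is absent at month 12 either way.

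**Conclusion.** The concern holds. As written, the primary outcome cannot measure the diet-alone contrast in the objective, because no woman is scheduled to be on placebo at the primary visit. This follows from the protocol's text and needs no assumption.

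The size of the loss is illustrative. With switched women reaching half to all of the drug effect, three-group power at 1 year is roughly 5% to 38%, or 5% to 49% with a baseline correlation of 0.5. The undiluted figures are 73% and 85%. The month-6 comparison and the 1-year metformin-versus-Avandamet comparison are both sound, but the first is not primary and the second is not what the sample size covers.

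**What to change.** Make change from baseline to 6 months in fasting and 1-hour insulin the primary comparison across the three randomised arms. Make the 12-month change secondary: metformin versus Avandamet among women randomised to them at baseline, with former placebo women reported separately by the drug they were moved to. State in Objective and Overview, Study Design and Drug Dose that the active arms continue to month 12.

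This costs wording only, with no added patients, visits or assays. With the arms intact at month 6, the sizing inputs apply as stated. The price is that 1-year durability is no longer a primary question.

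There are two alternatives, depending on what the sponsor wants:

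- **A 1-year placebo-controlled effect:** keep the placebo arm blinded on placebo to month 12. This costs 25 women six more months on placebo and risks more drop-out, which the power assumptions already expect to be high on placebo.
- **Metformin versus Avandamet at 1 year:** name that as the primary contrast and redo the sample size for two groups, with a justified difference between the drugs.

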|  | 
 
1. known diabetes, fasting blood sugar <math>\geq 110</math> mg/dl or HbA-1-C <math>\geq 6.0\%</math>
 
2. known hepatic disease or ALT <math>> 40</math>
 
3. known renal disease or creatinine <math>\geq 1.4</math>
 
4. known severe pulmonary disease
 
5. chronic acidosis of any etiology
 
6. Congestive heart failure (NYS Category 1), treated or untreated
 
7. a history of diagnosed or suspected coronary artery disease
 
8. Cancer – active within 5 years
 
9. current alcoholism or other substance abuse
 
10. co-morbid psychiatric disorder, which in the opinion of the screening physician would require concomitant psychotherapy as part of obesity management
 
11. currently untreated thyroid abnormality (TSH <math>\leq 0.2</math> or <math>\geq 4</math> mIU/L)
 
12. pregnancy or contemplation of pregnancy
 
13. use of TZD or metformin within the past year
 
14. allergy to TZD or biguanide
 
15. use of FDA approved or alternate obesity agent within 6 months of the study
 
16. history of pseudotumor cerebri
 
17. other impairment, such as a history of medication noncompliance, which in the judgment of the screening clinician, would preclude active study participation.
 
 |

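### The heart failure exclusion, as worded, covers one category only and leaves the others to general or discretionary criteria

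*Protocol*

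**What the plan says.** The exclusion list in the protocol's study design table has 17 items. Item 6 is the only one that names heart failure: "Congestive heart failure (NYS Category 1), treated or untreated". The abbreviation before the category number is not expanded anywhere in the text at hand.

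The items around it are:

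- Item 4: "known severe pulmonary disease"
- Item 5: "chronic acidosis of any etiology"
- Item 7: "a history of diagnosed or suspected coronary artery disease"
- Item 17, a general item for other impairments "which in the judgment of the screening clinician, would preclude active study participation"

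Two other places bear on who gets in. Inclusion criterion 1 opens "Healthy, non-diabetic women with" and goes on to the weight-gain requirement. The design overview says: "After obtaining consent, and additional screening for suitability, 80 patients will undergo glucose tolerance testing".

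**The concern.** A safety exclusion should state its full scope. Here the qualifier in brackets narrows the item to one category. The closing words about treatment widen it by treatment status but not by category. A screener who applies the item as written has an explicit instruction for Category 1 and silence on the rest.

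That does not fit the rest of the list. A trial that seeks healthy women and bars even suspected coronary disease would hardly aim to exclude heart failure in one category only. The item does not permit other categories; it fails to address them. Three clinical sites are screening, so a matter left to judgment can be settled differently from site to site.

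**Working it through.** No figure in the plan depends on this item, so the check is a reading of the criteria, followed by a count of planned exposure.

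**1. Does the wording of item 6 reach other categories?** The bracket contains no inequality sign, no range and no phrase such as 'or above'. Elsewhere the list marks scope openly:

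| Exclusion item | How scope is set |
|---|---|
| 1, 2, 3, 11 | Inequality signs on laboratory values |
| 4 | An adjective limits the item to severe disease |
| 5 | A phrase states that every cause is covered |
| 6 | One category named, with no sign and no phrase of breadth |

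The signs survive in items 1, 2, 3 and 11, so there is no ground for assuming that one was lost from item 6 when the text was extracted.

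**2. Does another criterion name heart failure?** No. None of the other 16 exclusions and none of the inclusion criteria does, and the term does not appear elsewhere in the protocol. Criteria naming heart failure: 1, limited as written to one category.

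**3. What else could exclude a woman in another category?**

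- *Inclusion 1.* The requirement to be healthy is mandatory but undefined. It cannot mean free of cardiovascular risk factors, because inclusion 5 requires either a raised blood pressure reading or blood pressure medication, or a lipid abnormality or lipid medication.
- *Suitability screening.* It is mentioned in the design overview, without criteria of its own.
- *Exclusion 7.* It applies only where coronary disease is diagnosed or suspected, so it does not reach heart failure of other origin.
- *Exclusion 17.* It rests on the screening clinician's judgment about taking part in the study, and its only example is medication noncompliance.

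Together these would probably keep most such women out. None is an explicit rule on heart failure.

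**4. Planned exposure to active drug.** Inputs: three arms (Objective and Overview of the Study), a target of 25 per group (Summary of sample size calculations), and reassignment of the placebo arm to active treatment after 6 months (Objective and Overview of the Study).

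- Randomised: 3 × 25 = 75
- On active drug from randomisation: 2 × 25 = 50
- Moved from placebo to active drug after 6 months, if they continue: 25
- Planned for active drug at some point, before attrition: 50 + 25 = 75 of 75

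This is total planned exposure. It is not an estimate of how many women the wording affects. That number would need a heart failure frequency in the screened population, which the protocol does not give.

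**The case against.** The strongest reply is that this is a slip of the pen with no practical consequence. Brackets elsewhere in the criteria hold operational thresholds, such as the TSH limits in exclusion 11 and the FSH limit in inclusion 3, so item 6 may be a threshold whose sign was left out. The reference to treated and untreated disease also points to a broad aim. A woman with diagnosed heart failure is not healthy in the ordinary sense, and that criterion is mandatory. To enrol her, a screener would have to overlook it, read the bracket as exclusive and decline to use item 17. The protocol also states no heart failure hazard of either drug, so the harm from one wrongly enrolled woman cannot be sized from it.

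Much of this stands. A floor at Category 1 is the likelier intent, the backstops are real, the frequency is likely low, and the size of any harm is not documented. But the parallel brackets carry their inequality signs and item 6 does not, so they do not settle its meaning. If all categories were meant, that is a reason to say so. The protocol itself treats heart failure as a ground for exclusion, so the case for stating the scope correctly needs no outside knowledge of the drugs.

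**Conclusion.** The concern holds. As written, the only heart failure exclusion names one category, and all others depend on an undefined word, unspecified screening or clinical judgment. It is a low-frequency, avoidable eligibility and safety risk that should be corrected. The protocol does not show that women in other categories would in fact be enrolled.

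The number affected cannot be derived. That it is likely small is a judgment, based on the age range of 35 to 55 and the other criteria. Endpoints, power and type I error are untouched. The conclusion rests on a literal reading of item 6 and on the absence of any other mention of heart failure in the protocol; it does not depend on what the drafters intended.

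**What to change.** Delete the bracket in item 6 and write: 'Congestive heart failure of any class, treated or untreated'. With the bracket gone, no classification has to be defined, and all sites apply the same rule. The cost is a few words in the exclusion list, a negligible effect on recruitment, and no change to the sample size or the analysis.
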